## Abstract

**Background:**

Posttraumatic stress disorder (PTSD) affects up to 25% of trauma-exposed adolescents; yet, access to evidence-based treatment remains limited in rural regions. Trauma-focused cognitive behavioral therapy (TF-CBT) is the first-line intervention, but structural barriers such as long travel distances and therapist shortages hinder implementation. Digital and blended formats may improve accessibility, but evidence for adolescents with PTSD is limited. Shame and self-criticism are common following interpersonal trauma and can reduce engagement; compassion-focused strategies target these mechanisms and aim to enhance emotional safety.

**Objective:**

This protocol outlines a pilot randomized controlled trial (RCT) evaluating the feasibility of delivering blended trauma-focused cognitive behavioral therapy with compassion (bTF-CBT-C) for adolescents with PTSD in routine clinical care. A secondary aim is to assess the acceptability of the intervention among adolescents and caregivers. In addition, the study explores patterns and variability in clinical outcomes to inform the design of a future noninferiority trial.

**Methods:**

A 2-arm parallel-group pilot RCT will randomize 40 adolescents (12‐17 years) with *DSM-5* (*Diagnostic and Statistical Manual of Mental Disorders* [Fifth Edition]) PTSD to bTF-CBT-C or standard TF-CBT in routine child and adolescent psychiatric services. The intervention includes an approximately 5-week web-based stabilization phase, followed by 7‐14 therapist-led sessions delivered primarily via videoconference, with some in-person sessions. Primary outcomes will assess feasibility (recruitment, retention, adherence, data completeness, and adverse events) and acceptability (satisfaction, alliance, and qualitative interviews). Exploratory outcomes include PTSD symptoms, self-compassion, emotion regulation, depression, anxiety, suicidality, and dissociation. Assessments will be conducted at baseline, poststabilization, posttreatment, and 6-month follow-up. Feasibility and acceptability will be summarized descriptively. Exploratory analyses using analysis of covariance and mixed effects models will estimate variance parameters, confidence intervals, and descriptive change trajectories without hypothesis testing. Qualitative data will be analyzed using reflexive thematic analysis.

**Results:**

Recruitment started in February 2026, and data collection is projected to be completed by December 2028. Feasibility and acceptability outcomes, along with exploratory clinical patterns, will be reported in accordance with the CONSORT (Consolidated Standards of Reporting Trials) extension for pilot and feasibility trials.

**Conclusions:**

Findings will inform the refinement of the intervention, the assessment of trial feasibility, and the selection of outcomes for a fully powered noninferiority RCT. The study will also contribute to understanding how compassion-focused strategies may support emotional safety and engagement in trauma-focused treatment for adolescents.

## Introduction

Posttraumatic stress disorder (PTSD) is a common and impairing condition affecting up to 25% of trauma-exposed adolescents worldwide [1,2]. Access to evidence-based trauma-focused psychological interventions remains uneven, particularly in sparsely populated regions. In northern Sweden, long travel distances, waiting lists, and limited access to trained therapists restrict timely care [3,4]. These barriers make it difficult for adolescents to engage in regular in-person treatment.

Beyond these structural constraints, adolescents living in rural northern Sweden face additional contextual challenges that influence both help-seeking and engagement in treatment. In small communities, concerns about stigma, confidentiality, and being recognized when visiting health services can limit access to care [5,6]. At the same time, qualitative research indicates ambivalence toward fully digital interventions, as these formats reduce practical demands but may also be experienced as emotionally distant [5]. These findings underscore the need for care models that combine accessibility with relational and emotional support, such as blended interventions [5-8].

These structural barriers may not only limit access to care but also influence psychological processes relevant to treatment engagement. For example, limited or disrupted access to trauma-focused interventions may exacerbate feelings of shame, isolation, and self-criticism, which are common following interpersonal trauma [9] and may reduce engagement in trauma processing.

Trauma-focused cognitive behavioral therapy (TF-CBT) is the recommended first-line treatment for youth with PTSD and has demonstrated strong efficacy across diverse populations [10,11]. However, its conventional face-to-face delivery can be difficult to scale in sparsely populated regions. Digital and blended interventions have been proposed to address these challenges by increasing flexibility and reach, but evidence for adolescents with PTSD remains limited [12]. This gap is particularly evident for interventions that integrate therapist support and explicitly target key psychological mechanisms such as shame and self-criticism [9,13,14].

Despite the increasing use of digital mental health tools, few trauma-focused mobile applications have been developed for adolescents, and even fewer have been scientifically evaluated [12,15]. Existing applications are rarely integrated into structured treatment programs. This highlights the need for scalable tools that support stabilization and emotion regulation while complementing therapist-led care.

In addition to these technological gaps, important psychological mechanisms remain insufficiently addressed. Shame and threat-based emotions are common across PTSD presentations and are particularly pronounced following interpersonal trauma [9,16]. These processes may be especially salient during adolescence, a developmental period characterized by heightened social sensitivity and identity formation [17-19]. They can interfere with engagement in trauma processing [9,16]. Compassion-focused therapy (CFT) provides a mechanism-based framework for addressing these processes by reducing shame, strengthening emotion regulation, and promoting affiliative soothing [20,21]. Early findings in young people suggest that compassion-based approaches may enhance engagement in treatment [22-24]. However, such strategies have not yet been systematically integrated into TF-CBT for adolescents with PTSD.

To address these gaps, a blended trauma-focused cognitive behavioral therapy intervention with integrated compassion-focused components (bTF-CBT-C) was developed. This manualized intervention combines mobile health components, including web-based stabilization modules and therapist-guided video sessions, with selected in-person meetings. The design aims to reduce practical barriers to care while maintaining therapeutic alliance and supporting engagement in trauma-focused work. The approach is informed by adolescents’ preferences in rural northern Sweden, emphasizing flexibility, relational support, and emotionally attuned care [5].

The intervention builds on 3 previous studies. First, a qualitative study of rural youths’ experiences of trauma therapy [5] informed the design of the blended format, including the emphasis on flexibility, relational support, and emotional attunement. Second, validation of the Compassionate Engagement and Action Scale for Youth – Swedish Version (CEASY-SE) [25,26] guided the selection of compassion-related outcome measures. Third, a pilot randomized controlled trial (RCT) of digital CFT for young people [22,23] informed the development and integration of compassion-focused modules within the intervention. Together, these studies provide empirical and theoretical foundations for the current trial.

Given the structural barriers to accessing trauma-focused treatment in rural regions, the primary aim of the blended intervention is to improve accessibility and scalability rather than to increase clinical efficacy. A noninferiority design is therefore appropriate to evaluate whether comparable clinical outcomes can be achieved while reducing barriers to care [27]. If outcomes are comparable to those of standard TF-CBT while requiring fewer in-person visits and reducing the travel burden, the intervention may provide important service-level advantages.

Although integration of compassion-focused strategies may enhance outcomes, the evaluation focuses on whether effectiveness can be maintained while improving access. Should clinically meaningful improvements be observed, alternative trial designs, such as superiority trials, may be considered.

In this context, the current pilot study will inform the design of a future noninferiority trial by providing estimates of recruitment, retention, outcome variability, feasibility, and acceptability, thereby reducing uncertainty in key design parameters. These will also support the selection of primary outcomes, estimation of sample size requirements, and specification of an appropriate noninferiority margin.

The aim of this pilot RCT will be to evaluate the feasibility and acceptability of delivering bTF-CBT-C to adolescents with PTSD within routine child and adolescent psychiatric services.

The objectives will be (1) to assess the feasibility of delivering bTF-CBT-C in routine care (eg, recruitment, retention, and adherence); (2) to evaluate the acceptability of the intervention (eg, satisfaction ratings and qualitative feedback); and (3) to explore patterns of change in clinical and mechanism-related outcomes, including estimation of variability to inform the design of a fully powered noninferiority trial.

## Methods

### Study Design

This pilot RCT will use a 2-arm parallel-group design with a mixed methods approach. The primary purpose of the trial will be to evaluate the feasibility and acceptability of delivering bTF-CBT-C compared with standard TF-CBT. Consistent with recommendations for pilot and feasibility trials, the study will not be powered to detect clinical effectiveness. The trial has been registered at ClinicalTrials.gov (ID: 2024-07057-01MixadTFKBT).

The trial will follow the updated SPIRIT (Standard Protocol Items: Recommendations for Interventional Trials) 2025 guidelines (Checklist 1) [28] for trial protocols and the CONSORT (Consolidated Standards of Reporting Trials) extension for pilot and feasibility trials [29]. A total sample size of 40 participants was selected as appropriate for a pilot feasibility trial. Similar sample sizes have been used in prior pilot studies of trauma-focused and blended psychological interventions, supporting their suitability for estimating feasibility outcomes in this context [30,31]. These participants (adolescents aged 12‐17 years meeting criteria for PTSD) will be randomized to either bTF-CBT-C or standard TF-CBT in routine child and adolescent psychiatric services.

The study adopts a convergent mixed methods design, in which quantitative feasibility and acceptability outcomes are collected in parallel with qualitative interview data [32,33]. Integration will occur at the interpretation stage, where qualitative findings will be used to contextualize and explain quantitative patterns (eg, recruitment, adherence, and satisfaction) and to identify convergences and discrepancies across data sources.

Assessment time points and weekly process measures will follow the predefined SPIRIT schedule (Table 1), with additional operational details provided in Multimedia Appendix 1.

**Table 1. T1:** SPIRIT^a^ schedule of enrollment, interventions, and assessments for the pilot randomized controlled trial bTF-CBT-C^b^ versus standard TF-CBT^c^.

Phase/activity	T0: baseline	T0a: allocation	T1: poststabilization	T2: postintervention	T3: 6-month follow-up
Enrollment					
Eligibility screening	✓				
Informed consent (youth + caregiver)	✓				
Baseline assessments	✓				
Randomization		✓			
Interventions					
bTF-CBT-C (experimental)		✓	✓	✓	✓
Standard TF-CBT (control)		✓	✓	✓	✓
Primary outcomes (feasibility)					
Recruitment rate	✓				
Retention rate			✓	✓	✓
Adherence (session attendance, module completion)			✓	✓	
Adverse events (youth, caregiver + therapist)			✓	✓	✓
Primary outcomes (acceptability)					
Satisfaction (youth + caregiver)				✓	
Therapeutic alliance (youth, caregiver, therapist)^d^			✓	✓	
Digital treatment evaluation (youth + caregiver)^d^			✓		
Exercise evaluation^d^			✓		
Qualitative interviews			✓	✓	✓
Exploratory and clinical outcomes					
PTSD^e^ symptoms (CATS-2^f^, CRIES-13^g^)	✓		✓	✓	✓
Dissociation (DSQ-12^h^)	✓			✓	✓
Self-compassion (CEASY-SE^i^)	✓		✓	✓	✓
Emotion regulation (DERS-16^j^)	✓			✓	✓
Depression/anxiety/suicidality (MADRS-Y^k^, RCADS^l^)	✓		✓	✓	✓
Progression criteria					
Recruitment ≥60%	✓				
Retention ≥70%			✓	✓	✓
Acceptability ≥4/5				✓	
Data completeness ≥80%			✓	✓	✓

a SPIRIT: Standard Protocol Items: Recommendations for Interventional Trials.

b bTF-CBT-C: blended trauma-focused cognitive behavioral therapy with compassion.

c TF-CBT: trauma-focused cognitive behavioral therapy.

d Repeated mechanism/process measures (eg, therapeutic alliance, digital treatment evaluation, exercise evaluation, shame visual analogue scale, Trauma-Related Shame Inventory/Trauma-Related Guilt Inventory) are collected throughout the stabilization and trauma phases. A detailed full schedule table with all weekly/mid-module assessments (T0-T9) is provided in Multimedia Appendix 1.

e PTSD: posttraumatic stress disorder.

f CATS-2: Child and Adolescent Trauma Screen, version 2.

g CRIES-13: Children’s Revised Impact of Event Scale, 13-item version.

h DSQ-12: Dissociative Symptoms Questionnaire, 12-item version.

i CEASY-SE: Compassionate Engagement and Action Scale for Youth – Swedish Version.

j DERS-16: Difficulties in Emotion Regulation Scale, 16-item version.

k MADRS-Y: Montgomery-Åsberg Depression Rating Scale for Youth.

l RCADS: Revised Child Anxiety and Depression Scale.

### Setting

The study will be conducted in child and adolescent psychiatry clinics in the regions of Norrbotten and Västerbotten in northern Sweden. These clinics provide publicly funded specialist mental health care for children and adolescents, including psychological and psychiatric assessment and treatment. All study procedures, including screening, recruitment, assessments, and intervention delivery, will be carried out within existing clinical infrastructure and coordinated by trained clinical staff at the participating units.

### Participants

#### Inclusion Criteria

Participants will be included if they meet the following criteria: (1) adolescents aged 12‐17 years; (2) *DSM-5* (*Diagnostic and Statistical Manual of Mental Disorders* [Fifth Edition]) PTSD diagnosis confirmed by the Mini-International Neuropsychiatric Interview for Children and Adolescents (MINI-KID) [7]; (3) score ≥25 on the Child and Adolescent Trauma Screen, version 2 (CATS-2) [8]; (4) a nonoffending caregiver willing to participate; and (5) ability to communicate in Swedish.

#### Exclusion Criteria

Participants will be excluded if they meet any of the following criteria:

Safety-related criteria: active psychosis, severe dissociative symptoms, and acute suicidality requiring inpatient care.Comorbidity-related criteria: autism spectrum disorder, severe eating disorder, severe obsessive-compulsive disorder, substance use disorder requiring treatment, and regular benzodiazepine use (>1 time/week).Logistical and treatment-related criteria: unstable living conditions or ongoing trauma exposure, cognitive impairments or medical conditions that prevent participation, concurrent trauma-focused psychotherapy, recent initiation or discontinuation of psychotropic medication (within 6 weeks), and planned medication changes during the study.

The exclusion criteria were selected to balance participant safety with the feasibility of delivering a blended trauma-focused intervention. Criteria related to acute suicidality, severe psychiatric comorbidity, and unstable living conditions were included to ensure that participants can safely engage in trauma-focused work. For example, recent changes in psychotropic medication and severe conditions such as eating disorders or obsessive-compulsive disorder were excluded to reduce clinical instability and potential confounding of treatment effects, particularly in a partially remote treatment format. Although these criteria may restrict eligibility in routine care, they were considered appropriate for this feasibility study in line with recommendations for pilot and feasibility studies [34]. Their impact on recruitment and external validity will be evaluated to inform future trials, including consideration of whether certain criteria may be modified or relaxed with appropriate monitoring strategies.

The study includes adolescents meeting *DSM-5* criteria for PTSD regardless of trauma type. Although compassion-focused mechanisms such as shame and self-criticism are particularly prominent in interpersonal trauma, these processes are also present across broader PTSD presentations. In specialist child and adolescent mental health services, where interpersonal and complex trauma exposures are common, these mechanisms are therefore relevant for a substantial proportion of participants. The intervention thus targets mechanisms that may be especially salient among adolescents exposed to interpersonal trauma while remaining theoretically and clinically relevant across broader PTSD presentations.

### Sample Size

As this is a pilot RCT, the sample size is set at 40 adolescents (20 per arm). This sample size is expected to enable estimation of key feasibility parameters, including recruitment, retention, adherence, and data completeness, as well as estimates of variability in outcome measures [34,35]. The selected sample size also reflects practical considerations related to recruitment within rural child and adolescent psychiatric services [36,37]. No formal power calculation will be conducted, as the trial is not designed to test intervention effectiveness but to inform the design and sample size planning for a future fully powered noninferiority trial.

### Ethical Considerations

The study will be conducted in accordance with the Declaration of Helsinki and applicable Swedish regulations governing research involving minors. Ethical approval has been obtained from the Swedish Ethical Review Authority (DNR 2024-07057-01, 2025-04566-02). Adolescents and caregivers will receive written and verbal information about study procedures, risks, benefits, confidentiality, and their right to withdraw from the study at any time without consequences to their clinical care. Written informed consent will be obtained from caregivers, and written assent or consent will be obtained from adolescents, depending on age and regional guidelines.

Data management will comply with the General Data Protection Regulation (GDPR) and institutional standards for handling sensitive personal data. All study data will be pseudonymized and stored on secure, access-restricted servers, with encrypted data transfer. Only authorized members of the research team will have access to identifiable data. Metadata and documentation will be prepared in accordance with the FAIR (findable, accessible, interoperable, and reusable) principles while ensuring that no identifiable information is publicly disclosed. Data will be retained in accordance with institutional requirements, and results will be disseminated through peer-reviewed publications and scientific presentations.

### Safety Procedures

A structured safety plan will be collaboratively developed with each adolescent and caregiver during the first therapist-led meeting, prior to the web-based stabilization phase. The plan will outline individualized strategies for managing distress, suicidal ideation, self-harm urges, and other safety concerns. It will include coping strategies, caregiver involvement, and clear instructions for contacting clinical staff during working hours or emergency services if risk escalates outside these hours.

During the web-based phase, suicide risk and distress will be monitored weekly via digital self-report measures completed by adolescents and caregivers. Reports indicating increased risk (eg, escalating distress, suicidal ideation, or self-harm urges) will trigger an alert to the clinical team. A clinician will review the alert within 1 working day, contact the adolescent and caregiver to assess risk, and initiate appropriate actions.

Therapists will follow a predefined protocol for managing interrupted or terminated video sessions. In the event of an unexpected disconnection, the therapist will first attempt to reconnect immediately, then contact the adolescent by telephone. If contact cannot be established, standard welfare-check procedures will be initiated, including contacting caregivers and, if necessary, coordinating with local services or emergency interventions.

Adverse events will be monitored through structured reports completed by adolescents, caregivers, and therapists, documenting occurrence and severity. All safety-related events, including suicide-related concerns, will be documented in a study safety log and reviewed in supervision. Serious adverse events (eg, suicide attempts, psychiatric hospitalizations, or significant clinical deterioration) will be reported to the principal investigator.

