### Digital Components

The bTF-CBT-C will use the CE-marked Amni web-based application [38] to deliver psychoeducation, digital exercises, and weekly self-report measures. Participants will access the application on their own smartphones or tablets. For example, adolescents and caregivers may engage with short films and guided audio-based exercises such as soothing rhythm breathing. They may also complete interactive self-compassion exercises that involve reflecting on self-critical thoughts or participate in brief gamified quizzes and tasks to reinforce learning and engagement. The application also includes ratings after exercises to capture engagement and perceived helpfulness. It collects symptom, process, and engagement data through secure, encrypted channels, providing real-time feedback to the clinical team. Screenshots from the application are provided in Multimedia Appendix 2.

Videoconferencing sessions will be conducted using GDPR-compliant platforms (Visiba Care and Platform24), integrated into routine clinical workflows. Technical support will be available through the clinic to assist participants with login issues, navigation, or other technical challenges related to digital components.

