### Interventions

#### Overview

The two interventions share the same theoretical foundation in TF-CBT and its PRACTICE (psychoeducation, relaxation, affective modulation, cognitive coping, trauma narrative/exposure, in vivo mastery, conjoint caregiver-child sessions, and enhancing safety and future development) components [10,42] but differ in delivery format, structure, and focus on mechanisms.

Standard TF-CBT is delivered as therapist-led, clinic-based treatment, with sessions conducted in person at the clinic. bTF-CBT-C is delivered as a blended intervention that combines therapist-led sessions with planned digital components and the systematic integration of compassion-focused strategies.

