#### Experimental Arm (bTF-CBT-C)

Participants randomized to the experimental arm will receive bTF-CBT-C. Treatment will consist of a blended intervention for adolescents and their caregivers that combines digital and therapist-led components, including therapist support during a web-based stabilization phase (via brief messaging and, if needed, stepwise escalation to telephone or videoconferencing) as well as approximately 7‐14 therapist-led sessions across the trauma processing and integration phases (primarily via videoconferencing with some in-person sessions). The intervention includes (1) a structured web-based stabilization phase, (2) systematic integration of digital modules throughout treatment, and (3) explicit incorporation of compassion-focused strategies targeting shame, self-criticism, and emotional safety. These mechanisms are expected to support engagement in trauma-focused work.

The intervention begins with an approximately 5-week stabilization phase delivered through structured web-based modules. Adolescents and caregivers have access to tailored application content relevant to their respective roles in treatment. This phase covers psychoeducation, relaxation, affective modulation, and cognitive coping and integrates compassion-focused strategies (eg, soothing rhythm breathing, compassionate imagery, and self-compassion exercises). Interactive exercises and nature-based mindfulness tasks aim to activate the soothing system and reduce threat-related responding. Gamified elements support engagement.

Following the stabilization phase, treatment continues with therapist-led trauma processing and integration components, including trauma narrative, cognitive restructuring, in vivo mastery, conjoint sessions, and safety planning, with caregiver involvement consistent with the TF-CBT model (C6-C9). Compassion-focused principles are applied throughout all phases of the intervention to support emotional safety and engagement.

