#### Primary Outcomes

##### Feasibility

###### Overview

Feasibility will be evaluated by assessing the extent to which the intervention and study procedures can be delivered within routine child and adolescent psychiatric services. Indicators will include recruitment rate, retention at each major assessment point, adherence to therapist-led and digital components, data completeness, and the functioning of study logistics such as randomization and assessment procedures. Adverse events will be monitored throughout the study via youth, caregiver, and therapist reports.

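### Suicide-related and distress events have an extra, alert-linked detection route in the experimental arm, and the shared safety log is not described as recording how each event was found

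*Protocol article*

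**What the plan says.** Safety Procedures sets up a weekly screen tied to one phase of treatment: "During the web-based phase, suicide risk and distress will be monitored weekly via digital self-report measures completed by adolescents and caregivers". It adds: "Reports indicating increased risk (eg, escalating distress, suicidal ideation, or self-harm urges) will trigger an alert to the clinical team". The phase belongs to the experimental arm. Under Experimental Arm (bTF-CBT-C) the article says: "The intervention begins with an approximately 5-week stabilization phase delivered through structured web-based modules". Digital Components likewise assigns the application to that arm: "The bTF-CBT-C will use the CE-marked Amni web-based application [38] to deliver psychoeducation, digital exercises, and weekly self-report measures". For the comparator, the Interventions overview says: "Standard TF-CBT is delivered as therapist-led, clinic-based treatment".

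The same safety section then names a single repository: "All safety-related events, including suicide-related concerns, will be documented in a study safety log".

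Separately, adverse events are a primary feasibility outcome in the Abstract, in Table 1 and under Primary Outcomes. The feasibility overview says: "Adverse events will be monitored throughout the study via youth, caregiver, and therapist reports". Adverse Event Monitoring specifies short weekly items answered by youth, caregivers and therapists, with severity rated 0-3, and has these events documented and reviewed under the safety procedures. None of this is restricted to one arm.

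**The concern.** When one arm is screened through a route that the other lacks, the number of events found depends on the screening as well as on the events. Here the extra route covers suicide-related concerns and distress, the events of most interest when asking whether a partly remote format is acceptable in safety terms. Study Design describes the primary purpose as assessing feasibility and acceptability of bTF-CBT-C against standard TF-CBT, so readers will look at safety events side by side.

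Alert-found concerns and events from the common items come under the same procedures, and nothing in the article separates them by how they were found. A table of logged events by arm would then mix two sources, one of them described for a single arm. If the route is not recorded when the entry is made, a later analysis may be unable to recover it.

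**Working it through.** The plan gives no event rate, detection probability or power figure for safety, so there is nothing to reproduce. The check sets the sections side by side and counts planned occasions.

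**Step 1. Who gets the alert-linked screen?** Safety Procedures ties it to the web-based phase. Digital Components and Experimental Arm (bTF-CBT-C) give that phase and the application to the experimental arm. Control Arm (Standard TF-CBT) describes weekly in-person sessions, with only occasional video contact, and no equivalent screen.

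**Step 2. How many extra occasions?** Inputs: a phase of about 5 weeks (Experimental Arm), weekly reporting by adolescents and caregivers (Safety Procedures), 20 participants per arm (Sample Size).
- Per experimental participant: 5 weeks x 1 per week = about 5 occasions.
- Across the experimental arm: 20 x 5 = about 100 participant-occasions, each with two respondents.
- Control arm: 0 described.

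These are screening opportunities, not events.

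**Step 3. Which routes are common to both arms, as written?**

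| Route | Section | Limited to one arm? |
|---|---|---|
| Weekly adverse-event items, three informants | Adverse Event Monitoring | No |
| Youth, caregiver and therapist reports throughout the study | Primary Outcomes, Feasibility | No |
| Structured reports, same three informants | Safety Procedures | No |
| Adverse-event row at T1, T2, T3 | Table 1 | No |
| MADRS-Y (includes a suicidality item) at T0-T3 | Table 1 | No |
| Weekly digital risk and distress reports with alerts | Safety Procedures | Yes, through the web-based phase |

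Five of the six routes carry no arm restriction. Only the last does.

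**Step 4. Do the routes meet?** Safety Procedures puts all safety-related events, suicide-related concerns included, in one log. Adverse Event Monitoring refers its own events to those same procedures. Alert-found and item-found events can therefore sit together with no marker of origin.

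**Step 5. Which way would a difference run?** Controls see a therapist in person each week. In Table 2, experimental modules C2 to C5 are self-paced with optional messaging. The digital screen could add detections beyond those in the control arm, or it could offset reduced therapist contact. The text does not settle which.

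**The case against.** A reader might infer that adverse events as a whole are ascertained unequally, or that the experimental arm will look less safe than it is. The documents support neither. The stated adverse-event instrument is weekly, comes from three informants and is not restricted by arm, and Table 1 schedules one adverse-event row for the whole trial. Weekly in-person contact is itself a detection route for controls, so the sign of any imbalance is open. This part of the objection stands.

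It can also be said that the log is described as material for supervision, and that no section names it as the source of the adverse-event outcome or plans a between-arm test on log counts. That is correct. Feasibility outcomes are summarised descriptively, and adverse events are not among the four Progression Criteria, so the decision to proceed does not rest on this comparison. It limits the consequence without removing the point. The two kinds of event share procedures and a log, and a descriptive table by arm is still read as a comparison.

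Finally, how controls complete the weekly items may be set out in Multimedia Appendix 1, which is not shown. Its absence from the article is no fault, and the point does not depend on it: even if the common items are identical in both arms, one arm keeps an additional route.

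**Conclusion.** The point holds in a limited form. As described, suicide-related and distress events have one more detection route in the experimental arm, for about 5 weeks, and what it finds enters the same log as other safety events. By-arm summaries of logged events of these types would be confounded by detection route. The size of the effect on counts cannot be derived from the documents, and its direction is not fixed. The consequence is confined to the descriptive safety comparison and does not reach the progression decision.

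This rests on two assumptions: that no equivalent alert-linked screen for controls appears in material not shown, and that log entries contribute to what is reported as adverse events. If either fails, the point falls away or becomes a matter of labelling. It is a cheap improvement, not a flaw that threatens the trial.

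**What to change.** 1. Add a detection-route field to the safety log now: common weekly item (and which informant), therapist contact, app alert, scheduled questionnaire, or other. Allow more than one route and mark the first, since follow-up of an alert may lead to the same event being reported on the common items. Trial Status gives 6 of 40 participants enrolled at submission. For entries already made, fill in the route where records allow and otherwise mark it unknown.
2. State that the by-arm adverse-event summary uses the common weekly items, with the same content, informants and frequency in both arms, plus serious adverse events. If Multimedia Appendix 1 already says this, a cross-reference is enough.
3. List events found only by app alert in a separate table for the experimental arm.

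The cost is one log field and one extra table, plus a short weekly form for controls if none is already planned. The change concerns recording and reporting only. Monitoring of risk and the clinical response to it are left as they are.
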